**Fig. 1 fig1:**
[figure not shown]
The flow chart of the trial.

This is a randomized controlled multicenter clinical trial comprising two parallel groups. From January 2024 to June 2025, 140 patients meeting the diagnostic criteria and syndrome types of UC will be recruited. During the recruitment process, potential participants meeting the inclusion criteria will be thoroughly informed about the study's purpose, examinations, intervention measures, and follow-up procedures. Upon obtaining informed consent, eligible subjects will be randomly assigned to two groups in a 1:1 ratio. The groups will receive either JPQC combined with mesalazine or mesalazine intervention for 12 weeks. The UC patients will be followed up again after 6 months. The schedule details are listed in Table 1.

**Table 1 tbl1:** Schedule of trial.

Period	enrollment	baseline	treatment			follow-up
time points	week-1	week 0	week 4	week 8	week 12	week 24
patients						
Informed consent	✓					
Inclusion/Exclusion criteria	✓					
Medical history	✓					
Physical examination	✓					✓
Laboratory examination	✓					✓
Randomization	✓					
Intervention						
Jianpi Qingchang decoction(JPQC) group	JPQC:two times daily; + mesalazine: 1g/three times daily					
Mesalazine control group	1g/three times daily					
Outcomes						
Inflammatory bowel disease fatigue scale(IBD-F)		✓	✓	✓	✓	✓
Inflammatory Bowel Disease Questionnaire (IBDQ)		✓	✓	✓	✓	✓
TCM symptom efficacy		✓	✓	✓	✓	✓
Modified Mayo score		✓			✓	✓
Simple clinical colitis activity index (SCCAI)		✓				
Intestinal microbial diversity and non-targeted metabonomics		✓			✓	
Trial evaluation						
Safety of medicine		✓	✓	✓	✓	✓
Adverse event		✓	✓	✓	✓	✓
Reasons of drop-outs or withdrawals		✓	✓	✓	✓	
Patient's compliance					✓	

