### Safety outcomes

2.6

The main safety indicators include laboratory tests before and after treatment, encompassing blood routine, urine routine, fecal routine, occult blood, liver and kidney function, and electrocardiogram.

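### Table 1 ticks laboratory tests only at week -1 and week 24, which does not fit section 2.6's before-and-after comparison for a 12-week treatment, and the undefined safety row does not settle it

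*Protocol article*

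**What the plan says.** Section 2.1 fixes the length of treatment: "The groups will receive either JPQC combined with mesalazine or mesalazine intervention for 12 weeks". It then adds one later visit: "The UC patients will be followed up again after 6 months". Table 1 shows that visit as week 24, under the follow-up period.

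Section 2.6 describes the safety assessment: "The main safety indicators include laboratory tests before and after treatment". The panel it lists takes in blood, urine and stool tests, occult blood, liver and kidney function, and an ECG. It attaches no week number to either time point.

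Two rows of Table 1 bear on when these tests are done:

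- "Laboratory examination" is ticked at week -1 and week 24, and is blank at weeks 0, 4, 8 and 12.
- "Safety of medicine" is ticked at weeks 0, 4, 8, 12 and 24. Neither the table nor the text defines what it contains.

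Adverse events have their own row, also ticked at weeks 0, 4, 8, 12 and 24.

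**The concern.** A before-and-after safety comparison for a 12-week treatment would be expected to use a value from the end of those 12 weeks. The only row named for laboratory tests has none. Its single post-baseline tick falls at the follow-up visit, when patients have been off trial treatment for some time.

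Safety is one of the trial's stated aims (Introduction and abstract). If the laboratory row is the schedule that sites follow, a change in liver or kidney values during exposure could resolve before anyone measures it. A patient who leaves before week 24 would contribute no post-baseline laboratory value. Section 2.2.5 lists allergy or a serious adverse reaction among the reasons for withdrawal, so the patients without a value may include those in whom one would be most informative. A sample not taken at week 12 cannot be recovered at analysis.

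There is also a consistency risk. Section 2.2.1 names three recruiting hospitals, and each could read the two rows differently.

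**Working it through.** The plan gives no figure to reproduce. The check sets the table and the text side by side, with one subtraction.

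**Inputs**

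| Item | Source | Visits or value |
|---|---|---|
| Treatment duration | Section 2.1 | 12 weeks |
| Laboratory row | Table 1 | week -1, week 24 |
| Physical examination row | Table 1 | week -1, week 24 |
| Safety-of-medicine row | Table 1 | weeks 0, 4, 8, 12, 24 |
| Adverse event row | Table 1 | weeks 0, 4, 8, 12, 24 |
| Microbiome and metabolomics row | Table 1 | weeks 0, 12 |
| Timing of laboratory tests and ECG | Section 2.6 | before and after treatment, no week given |
| Timing of microbiome and metabolomics | Section 2.5; abstract | before and after treatment; baseline and 12 weeks |

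**Step 1. What the protocol means by after treatment.** Section 2.5 uses the same before-and-after wording as section 2.6. For the section 2.5 outcomes, Table 1 and the abstract both place the second measurement at 12 weeks. On the protocol's own usage, after treatment means week 12.

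**Step 2. Reading A: the laboratory row governs.** Scheduled tests fall at week -1 and week 24. The number of ticks from week 0 to week 12 is 0. The interval from end of treatment to the only post-baseline sample is 24 - 12 = 12 weeks. This conflicts with the usage found in step 1.

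**Step 3. Reading B: the safety row includes the section 2.6 tests.** Tests would then fall at weeks 0, 4, 8, 12 and 24. The interval from end of treatment to the nearest sample is 12 - 12 = 0 weeks. Reading B does not fit cleanly either. Five time points are more than a before-and-after pair, the laboratory row would duplicate the safety row at week 24, and its blanks at weeks 0 to 12 would be wrong.

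**Step 4. Comparison.** Reading A leaves the laboratory row at odds with section 2.6 as the protocol uses the phrase. Reading B leaves the two rows of Table 1 at odds with each other. Under either reading the printed passages need reconciling.

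**Limit of the 12-week figure.** It uses Table 1's week 24. Section 2.1 does not say whether its 6 months run from randomisation or from the end of treatment. If they run from the end of treatment, the gap under reading A is longer.

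**The case against.** The strongest reply is that the safety row already supplies the missing visits. It stands apart from the adverse event row, so it should mean something other than recording adverse events, and the only specific safety indicators the article names are the section 2.6 tests. On that view tests take place at week 12, and the laboratory row merely shows screening and follow-up. This reply stands in part. Because the reading is possible, a reader who infers from the laboratory row that no laboratory test is scheduled during exposure, or that the safety comparison will use week 24 samples, goes further than the documents allow. The reply does not close the matter, because the row is undefined and the reading brings the misfits shown in step 3.

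Three other stronger inferences are also unsupported:

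- **A count of patients with no value.** Applying the 20% dropout in section 2.2.6 to 140 patients gives 0.20 × 140 = 28. That percentage is a whole-trial sample-size allowance with no timing, so it does not estimate losses between weeks 12 and 24. Patients who leave before week 12 would miss a week 12 sample as well.
- **No safety observation during treatment.** Table 1 schedules adverse event recording at weeks 4, 8 and 12, and section 2.2.5 provides for withdrawal after allergy or a serious adverse reaction. Only the laboratory and ECG part is unclear.
- **A false reassurance in the report.** Nothing in the article says the trial will claim that no laboratory signal was found.

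It can also be said that an article condenses a fuller protocol. That does not answer this point, since the ticks and the definition are both printed and do not agree. It is true that the primary outcome, the IBD-F fatigue scale, is unaffected.

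**Conclusion.** The point holds as an unreconciled schedule for the trial's main safety indicators. The laboratory row has no tick during or at the end of the 12-week treatment, section 2.6 calls for values before and after treatment, and section 2.5 shows that the protocol uses that wording for week 12. The safety row does not decide between the two.

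The size depends on the reading. If sites follow the laboratory row, the first post-baseline values come 12 weeks after treatment ends, taking week 24 from Table 1, and patients lost before then have none. If the safety row includes the tests, the gap is 0 weeks and the fault is one of labelling. The documents do not show which applies, and they give no basis for counting the patients affected. The matter should be settled before sites rely on the table, because missed samples cannot be replaced later.

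**What to change.** Reconcile Table 1 with section 2.6:

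1. State which tests the safety-of-medicine row covers and how it relates to the laboratory row.
2. Show the after-treatment laboratory and ECG assessment at the existing week 12 visit, in line with the protocol's own use of the phrase in section 2.5.
3. Name week 12 in section 2.6 as the visit compared with baseline.
4. Keep the week 24 tick as follow-up. Moving it to week 12 would remove the only follow-up sample on that row, and nothing in the article suggests that the sample is unwanted.

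The cost is a correction to one table and one sentence. If the tests are not already done at week 12, add at most one routine panel per patient, covering the tests listed in section 2.6 (blood, urine, stool, occult blood, liver and kidney function, ECG), at a visit already scheduled. If the safety row already includes them, there is no added cost to patients or sites.

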**Methods:**

In this randomized clinical trial, 140 subjects diagnosed with UC will be recruited and randomized into two groups. They will receive either JPQC combined with mesalazine or mesalazine alone for 12 weeks. Follow-up visits will be conducted every four weeks, with a post-treatment visit scheduled at 6 months. The primary outcome measures include the Inflammatory bowel disease fatigue scale(IBD-F). Secondary efficacy indicators comprise the assessment of TCM syndrome and individual syndrome efficacy before and after treatment, Modified Mayo score, Simple clinical colitis activity index (SCCAI), as well as the Inflammatory Bowel Disease Questionnaire (IBDQ) for each group. The other outcomes are the Intestinal microbial diversity and non-targeted metabonomics, which will be measured at baseline and 12 weeks after randomization.

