#### Secondary outcomes

2.4.2

The secondary outcomes include the following items.

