##### The disease activity

2.4.2.3

The modified Mayo score [15] and simple clinical colitis activity index (SCCAI) [22] will be recorded to assess the disease activity.

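### Table 1 schedules the SCCAI at baseline only, although the article makes it a secondary efficacy outcome

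*Protocol article*

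**What the plan says.** The abstract (Methods) counts the SCCAI among the secondary measures of efficacy, in the run "Modified Mayo score, Simple clinical colitis activity index (SCCAI), as well as the Inflammatory Bowel Disease Questionnaire (IBDQ) for each group".

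Section 2.4.2 opens with "The secondary outcomes include the following items". Under it, section 2.4.2.3 pairs the SCCAI with the modified Mayo score and says that the "simple clinical colitis activity index (SCCAI) [22] will be recorded to assess the disease activity". That section gives no visit times.

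For timing, section 2.1 sends the reader to one place: "The schedule details are listed in Table 1". In Table 1 the row labelled "Simple clinical colitis activity index (SCCAI" is ticked at week 0 and nowhere else. The row directly above it, "Modified Mayo score", is ticked at weeks 0, 12 and 24.

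On treatment, section 2.1 states: "The groups will receive either JPQC combined with mesalazine or mesalazine intervention for 12 weeks".

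**The concern.** An efficacy outcome needs at least one value taken after treatment has started. The printed schedule gives the SCCAI none, so the outcome list and the schedule cannot both be right.

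What is at stake is one declared secondary outcome. If sites and the case report form follow Table 1, the final report can give a baseline SCCAI by group and nothing more. No later analysis plan can repair this.

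**Working it through.** No sample-size or power figure is involved. The check is to read the schedule row by row and then look for any text that overrides it.

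**Step 1: read the rows.** The Table 1 columns are weeks -1, 0, 4, 8, 12 and 24, which gives four post-baseline visits (4, 8, 12, 24).

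| Outcome row | Ticked weeks | Post-baseline visits ticked |
|---|---|---|
| IBD-F | 0, 4, 8, 12, 24 | 4 of 4 |
| IBDQ | 0, 4, 8, 12, 24 | 4 of 4 |
| TCM symptom efficacy | 0, 4, 8, 12, 24 | 4 of 4 |
| Modified Mayo score | 0, 12, 24 | 2 of 4 |
| SCCAI | 0 | 0 of 4 |
| Microbial diversity and metabonomics | 0, 12 | 1 of 4 |

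The SCCAI is the only outcome row with no post-baseline tick.

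**Step 2: is the row damaged?** In the text as read, the SCCAI row has its label plus six visit cells, seven in all. The IBD-F and modified Mayo rows also have seven and line up correctly with the column headings. The single SCCAI tick falls under week 0. A broken table is therefore an unlikely explanation, although a tick lost in typesetting cannot be fully excluded.

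**Step 3: does any text override the table?** The SCCAI is otherwise mentioned only in the abstract and in section 2.4.2.3. Section 2.4.2.3 gives no time point. In the abstract, the words "before and after treatment, Modified Mayo score, Simple clinical colitis activity index (SCCAI" might seem to promise SCCAI values on both sides of treatment. Grammatically, though, the timing phrase belongs to the TCM syndrome assessment that precedes it, so it does not clearly set a post-treatment SCCAI visit.

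**Step 4: what follows.** Week 0 is the baseline column, and the treatment period runs to week 12. On the assumption that week 0 assessments precede the first dose, the only scheduled SCCAI value cannot reflect treatment. A change score needs a value at some week t > 0, and so does a between-group comparison at week t. The schedule supplies none, so 0 of 140 patients would have either.

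**The case against.** The strongest reply is that nobody chose this. The abstract and section 2.4.2.3 plainly treat the SCCAI as an efficacy outcome, and one row of a condensed article table has probably lost its ticks. The full protocol and case report form may be correct. That is likely, and it is why the point is a contradiction to be reconciled and not a criticism of a deliberate design. It does not remove the point: the article prints a visit-by-visit schedule and refers to it for the details, and that schedule contradicts the stated role of the outcome. The count of 0 of 140 holds only if the table is followed literally. It restates the missing ticks and is not a separate measure of harm.

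A second reply is that little is lost, because section 2.4.2.3 uses two scales for the same purpose and the modified Mayo score is kept at weeks 12 and 24. This stands, and it limits the severity. The primary outcome, the sample size and the randomisation do not depend on the SCCAI.

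A reader might also draw stronger conclusions that the article does not support:

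- *That the trial loses its disease-activity index at weeks 4 and 8.* Neither the SCCAI nor the modified Mayo score is scheduled then, so nothing planned is lost. Bowel symptoms are still recorded at those visits through the TCM symptom score (section 2.4.2.2) and the intestinal dimension of the IBDQ (section 2.4.2.1).
- *That the SCCAI is needed to show that fatigue improves independently of colitis activity.* Section 2.7 plans no activity-adjusted or mediation analysis, and no stated objective calls for one. The introduction reports disease activity as associated with the risk of fatigue; it does not present it there as the cause.

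**Conclusion.** The contradiction is real. Table 1 schedules the SCCAI at week 0 only, while the abstract and sections 2.4.2 and 2.4.2.3 make it a secondary efficacy outcome. Followed as printed, the schedule leaves no patient with a post-treatment SCCAI and no estimable treatment effect on it.

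The size is limited: one secondary outcome, probably through an omission in the table, with post-treatment disease activity still measured by the modified Mayo score. It should be fixed, but it does not threaten the primary result.

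The conclusion assumes that the table text is intact, which the cell count supports, and that the sites' working schedule matches Table 1, which the article alone cannot show.

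**What to change.** Reconcile Table 1 and the case report form with the abstract and section 2.4.2.3.

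- **If the SCCAI is an efficacy outcome,** tick it at weeks 12 and 24, to match the modified Mayo score. Adding weeks 4 and 8 is optional; nothing in the article requires it.
- **If it was meant only as a baseline descriptor,** say so and remove it from the secondary outcomes in the abstract and section 2.4.2.3.

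The first option needs no new visits. It adds at most 140 × 2 = 280 assessments. If the full 20% dropout allowed for in section 2.2.6 occurred before week 12, the figure would be 140 × 0.80 × 2 = 224. Each should take a few minutes of scoring. The second option costs only a text change. If the full protocol and case report form already schedule the SCCAI after baseline, correcting the published table is enough.

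Make the change before patients reach week 12, since a missed score cannot be reconstructed.

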### Participants

2.2

#### Recruitment

2.2.1

Patients will be recruited from the outpatient and inpatient gastrointestinal endoscopy departments of Shanghai Hospital of Integrated Traditional Chinese Medicine, Longhua Hospital affiliated with Shanghai University of TCM and Traditional Chinese Medicine Hospital of Shaanxi Province.

#### Inclusion criteria

2.2.2

1)Age between 18 and 70 years old, both male and female.2)Diagnosis of ulcerative colitis confirmed by electronic colonoscopy and pathology, meeting the criteria established by the consensus on the diagnosis and treatment of inflammatory bowel disease (2018 Beijing) [15].3)Adherence to the 2018 Guidelines for Diagnosis and Treatment of Ulcerative Colitis, a Common Disease of Digestive System [16], TCM Syndrome Differentiation Criteria for spleen deficiency and dampness-heat syndrome.4)Underwent enteroscopy within the past 1 year.5)Absence of serious heart, liver, kidney, and other significant organ and blood system diseases.6)Full understanding of the purpose and content of the test, good compliance, and voluntary signing of the informed consent form.

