## Introduction

1

Ulcerative colitis (UC) is a chronic, non-specific inflammatory intestinal disease primarily affecting the colorectal mucosa and submucosa, categorized under inflammatory bowel disease (IBD). It is estimated that the global prevalence of ulcerative colitis will reach 5 million cases in 2023, with a rising incidence worldwide [1]. The main clinical symptoms of UC include persistent or frequent episodes of diarrhea and mucous purulent and bloody stools. These symptoms may be accompanied by systemic manifestations such as abdominal pain, acute diarrhea, and fatigue.

Fatigue, characterized by a disproportionate lack of energy or exhaustion to physical exertion, adversely affects daily activities and cannot be alleviated by rest [2]. It is a multifaceted, multifactorial symptom associated with various chronic diseases [3]. Notably, Fatigue is a significant clinical symptom for patients with IBD [4], reaching a prevalence of 86 % in those with active IBD and 50 %–52 % in those with mild to inactive IBD [5]. In Chinese patients with UC, the prevalence rate of fatigue is 61.8 %, with higher rates in active disease (68.2 %) than in remission (40.0 %). Factors such as Montreal classification, disease activity, and anxiety are linked to an increased risk of fatigue risk Background [6]. The presence of fatigue in patients with UC is associated with a diminished quality of life [7]. Addressing fatigue is crucial not only for improving the care and quality of life for patients with UC but also for reducing direct medical expenses and the indirect economic impact on work productivity and function [8]. Therefore, it is particularly important to find practical and effective ways to intervene fatigue for improving the care and quality of life of patients with UC.

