Traditional Chinese medicine (TCM) posits that the weakness of the spleen and stomach, exogenous pathogens, improper diet, and emotional disorders can contribute to UC. The disease primarily affects the large intestine and is characterized by spleen deficiency, and dampness-heat, blood stasis, and phlegm-dampness. UC is further categorized into seven syndrome types, such as spleen deficiency and dampness accumulation syndrome, large intestine damp-heat syndrome, excessive heat toxin syndrome and liver depression and spleen deficiency syndrome, with spleen deficiency and dampness accumulation syndrome and large intestine damp-heat syndrome being common [9]. In our previous study, we observed varying degrees of fatigue symptoms in patients with damp-heat syndrome of the large intestine and spleen deficiency and dampness accumulation syndrome. Fatigue was notably more prevalent and severe in the latter. Patients with UC and damp-heat syndrome of the large intestine exhibited symptoms such as "stagnation of wetness-evil," characterized by a heavy head, heavy body sleepiness, and sore limbs, among which heavy body sleepiness is its representative symptom. In contrast, patients with UC with spleen deficiency and dampness accumulation syndrome manifested "weakness" symptoms, including listlessness, fatigue, and weakness of limbs, among which fatigue and weakness are its characteristic symptoms. This finding holds significant guidance for clinical syndrome differentiation and the treatment of UC-related fatigue. The methods involving clearing heat and eliminating dampness, invigorating the spleen, and benefiting qi, as explored in this study, offer valuable insights into therapeutic approaches for managing UC-related fatigue [10]. Guided by the principles of invigorating the spleen and qi, clearing away heat and toxic materials, cooling blood and stopping bleeding, and regulating qi and relieving pain, we formulated and optimized Jianpi Qingchang decoction (JPQC) consisting of *Astragalus membranaceus (Huang Qi)30**g, Portulaca oleracea (Ma Chi Xian)30g, Codonopsis pilosula (Dang Shen)15g, Coptidis Rhizoma (Huang Lian)3 g, Sanguisorba officinalis (Sheng Di Yu)15g, Panax notoginseng (San Qi)6g, Bletilla striata (Bai Ji)3g, Radix Aucklandiae (Mu Xiang)6g, and Radix Glycyrrhizae (Sheng Gan Cao)6g* [11]. Forty-four phytochemicals, including astragaloside A, oleracein A, and coptisine, were identified from JPQC using the ultra-high performance liquid chromatography-quadrupole time-of-flight mass spectrometry (UPLC-Q-TOF/MS) method [12]. Our previous study revealed that JPQC effectively alleviated clinical symptoms of abdominal pain and diarrhea in patients with mild-moderate UC, improved mental fatigue, and increased quality of life [13,14]. However, there is a limited exploration of the impact of JPQC on fatigue in patients with UC with spleen deficiency and dampness-heat syndrome. Consequently, we have designed a randomized controlled clinical trial to comprehensively investigate the effectiveness and safety of JPQC in treating patients with UC with spleen deficiency and dampness-heat syndrome accompanied by fatigue. This research aims to contribute valuable insights into potential therapeutic interventions for addressing fatigue in patients with UC, particularly those with spleen deficiency and dampness-heat syndrome.

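### Eligibility sets no disease-activity range and the stated t-test ignores activity, although the protocol itself reports that fatigue, the primary outcome, varies with it

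*Protocol article*

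**What the plan says.** Section 2.2.2 (Inclusion criteria) lists six criteria. Three bear on the disease: "Diagnosis of ulcerative colitis confirmed by electronic colonoscopy and pathology"; "TCM Syndrome Differentiation Criteria for spleen deficiency and dampness-heat syndrome"; and "Underwent enteroscopy within the past 1 year". The nine exclusions in Section 2.2.3 cover recent drugs, other conditions and investigator judgement. Neither list names remission, active disease, a severity grade, or a modified Mayo or SCCAI limit.

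On who may be approached, Section 2.2.1 says: "Patients will be recruited from the outpatient and inpatient gastrointestinal endoscopy departments".

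On fatigue and activity, the Introduction gives an overall prevalence of 61.8% in Chinese patients with UC, "with higher rates in active disease (68.2 %) than in remission (40.0"%), and lists disease activity among the factors linked to fatigue. On earlier evidence, it says that JPQC "alleviated clinical symptoms of abdominal pain and diarrhea in patients with mild-moderate UC". That is the article's only mention of a severity range, and it describes an earlier study.

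In Section 2.4.2.3 the modified Mayo score and SCCAI "will be recorded to assess the disease activity", as secondary outcomes. Section 2.7 compares means with two-sample t-tests. Table 1 places randomisation at week -1 and the first modified Mayo and SCCAI at week 0.

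**The concern.** IBD-F is the primary outcome, and by the protocol's own account disease activity is a risk factor for fatigue. A known prognostic factor can be handled in three ways: restrict it at entry, balance it at randomisation, or adjust for it in the analysis. The printed eligibility does not restrict it, and the stated comparison of means does not adjust for it. The article gives only a 1:1 ratio for randomisation.

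Three things are at stake:

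- **Precision.** Variation in IBD-F that activity explains stays in the error term.
- **Secondary effects.** A patient in remission has little room to improve on modified Mayo, or on main TCM symptoms such as diarrhoea and bloody stool.
- **Target population.** A reader of the result could not tell which range of UC it applies to, or whether that range matches the mild-moderate patients of the cited earlier work.

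**Working it through.** **1. Does any criterion act as an activity limit?**

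| Criterion | Bearing on remission | Bearing on severe UC |
|---|---|---|
| UC diagnosis (2.2.2) | none | none |
| TCM syndrome (2.2.2) | may remove quiescent patients; its content is in a cited source | no ceiling stated |
| Endoscopy within 1 year (2.2.2) | no required finding, may be old | no required finding, may be old |
| Drug exclusions, 4 weeks (2.2.3) | none | removes some cases, no grade |
| Severe haemorrhagic disease, obstruction, perforation (2.2.3) | none | removes some cases, no grade |
| Investigator judgement (2.2.3) | open-ended | open-ended |

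No row sets a minimum or a maximum.

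**2. How many could be in remission?** Inputs from the Introduction: fatigue 61.8% overall, 68.2% active, 40.0% remission. With active share a:

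68.2a + 40.0(1 − a) = 61.8, so a = (61.8 − 40.0)/(68.2 − 40.0) = 21.8/28.2 = 0.773.

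Check against the stated overall figure: 0.773 × 68.2 + 0.227 × 40.0 = 52.7 + 9.1 = 61.8.

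- Remission share in that population: 0.227, and 0.227 × 140 = 32 patients.
- If all enrolled are fatigued: 0.227 × 0.400/0.618 = 0.147, and 0.147 × 140 = 21 patients.
- If the syndrome criterion removes every quiescent patient: 0.

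The range to carry is 0% to about 23%. The upper end ignores selection by TCM syndrome.

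**3. Dilution of modified Mayo and TCM-symptom effects.** Assume that patients in remission show no treatment difference on these outcomes. The average effect is then (1 − r) times the effect in active patients: a reduction of 0% at r = 0, 14.7% at r = 0.147 and 22.7% at r = 0.227. SCCAI is left out because Table 1 schedules it at baseline only.

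**4. Precision on fatigue.** The documents give no correlation between activity and IBD-F score. The Introduction's figures do give the share of variance in fatigue (yes/no) explained by activity (active or remission):

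a(1 − a)(0.682 − 0.400)² / [0.618 × (1 − 0.618)] = 0.1754 × 0.0795/0.2361 = 0.059.

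That is about 6% in that population, and nothing if no patient in remission is enrolled. A graded score such as SCCAI may explain more. This is an order of magnitude for a yes/no measure, not an estimate for IBD-F.

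**5. Chance imbalance.** Assume simple randomisation, which the article does not state, with 70 per arm and r = 0.227. The SD of the between-arm difference in remission share is √(2 × 0.227 × 0.773/70) = 0.071, so the 95% range is ±1.96 × 0.071 = ±0.14. A 14-point gap would shift expected fatigue prevalence by 0.14 × 28.2 = 3.9 percentage points.

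**The case against.** The stated objective is UC with this syndrome and fatigue, not active UC, so broad eligibility fits it. Patients in remission can be fatigued (40.0% in the Introduction) and can improve on IBD-F. An average effect over a mixed population can be interpreted. The remission share in an unselected UC population is not the share in this trial, because the syndrome criterion may imply current bowel symptoms. Section 2.2.3 already removes some severe cases, and recruiting inpatients does not show that severe UC is enrolled. All of this stands. It is why the remission share is given as a range from zero, and why restricting eligibility is not urged here.

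Three stronger readings are tempting and are not supported:

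- **That activity confounds the fatigue comparison.** Allocation is random, so activity is balanced on average, and chance imbalance is already covered by the test's error rate. The cost is precision, not bias.
- **That the trial loses its planned power.** On the planning rates (71% and 94.12%, 56 per arm), suppose a share r of each arm responds at the control rate. The experimental rate becomes (1 − r) × 0.9412 + r × 0.71, which is 0.907 at r = 0.147 and 0.889 at r = 0.227. Power at two-sided 0.05 would then fall from 90.8% to 76.3% or 66.0%. (Two-sided is used because the plan's formula gives 56.6 that way, near its 56, against 46.1 with the one-sided level it states.) This assumes no treatment effect in remission, an unselected remission share, and an effective rate in place of IBD-F. The documents support none of these.
- **That severe patients lie outside all earlier JPQC experience.** Only one strand of the cited work is labelled mild-moderate. The Discussion cites other work with no severity given.

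Stratification and covariates may also be set out in a fuller protocol or analysis plan. The point does not rest on that silence. It rests on the printed eligibility lists and on the comparison that Section 2.7 does state.

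**Conclusion.** The point holds in limited form. The eligibility lists leave activity open at both ends, and the stated comparison of means does not use it, although the protocol names it as a risk factor for its primary outcome. The effect on IBD-F is probably modest. On the Introduction's yes/no figures, activity explains about 6% of the variance in fatigue, and no IBD-F figure is available. Modified Mayo and TCM-symptom effects could shrink by 0% to about 23%, assuming patients in remission cannot improve on them and depending on how many the syndrome criterion lets in. The definition of the population suffers whatever that share is. The change is still worth making, because the adjustment uses data already scheduled and costs almost nothing.

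**What to change.** 1. In Section 2.7, replace the t-test for the primary outcome with a model for week-12 IBD-F, for example ANCOVA, with treatment, baseline IBD-F and one named baseline activity score (modified Mayo or SCCAI). Both scores are already collected at week 0. State that they are recorded before the first dose. The cost is a sentence in the plan.
2. Report the activity mix enrolled, by arm, and limit the conclusion to that range. No extra data are needed.
3. Optionally, stratify the 1:1 randomisation by activity and keep the stratum in the model. The downside is small but real: Table 1 randomises at week -1 and first scores activity at week 0, so the SCCAI or modified Mayo assessment would have to move ahead of randomisation.
4. The sponsor should decide whether eligibility is meant to cover all activity levels, say so in Section 2.2.2, and reconcile that with the mild-moderate evidence cited in the Introduction. Restricting entry would narrow the population and may slow recruitment. Which range to choose is a clinical decision, and none is proposed here.
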